### Treatment allocation and blinding

After eligibility has been assessed and informed consent has been obtained the infant will be enrolled in the study. To randomise an infant to the study, investigators will log in to the electronic Case Report Form (eCRF) and follow the prompts to input infant data. Only investigators specifically trained to perform randomisation will have access to the eCRF. Based on the order in which infants enter the study and stratified by sex, the infant will be assigned a randomisation number by the eCRF system. The infant will receive the product with the code corresponding to his/her randomisation number. Twins and multiple births will be allocated to the same study group. Investigators, all site staff including medical and nursing staff and supporting staff who prepare the infant feedings, and parents will be unaware of treatment allocation.

The randomisation sequence will be generated using the PLAN procedure of SAS statistical software (Enterprise Guide version 4.3 or higher) by a statistician from Danone Nutricia Research who has no further involvement in the conduct of the trial. The permuted block randomisation will be stratified by sex (boys, girls) with a 1:1 allocation ratio of test and control product. The block size or sizes and whether the block size(s) will be fixed or randomly varied will be decided by and known only to the statistician. The packaging of the test and control products will be identical in appearance. The study product for each infant will be labelled using a unique random number according to the randomisation schedule. These random numbers will have been linked (via a code) beforehand to either test or control product. Which numbers correspond to which treatment will only be known to the supplies manager at Danone Nutricia Research.

The randomisation code will be broken after analysis of the primary outcome and other outcomes collected until TEA. Assessors, parents, hospital staff and all those involved in the conduct and/or decision making of the follow-up phase will remain blinded to study product allocation until follow-up database lock after the last infant has completed the study (24 months corrected age). In the case of a medical emergency that requires preliminary unblinding of study product, unblinding in the eCRF or with sealed unblinding envelopes stored at the UMC Utrecht will be possible.

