### Sample size calculation

The sample size needed for TBSS analyses has been estimated based on previous simulations of the sensitivity of TBSS for detecting treatment effects, as reported by Ball et al., who recruited infants with GA < 36 weeks who underwent successful DTI at TEA (baseline characteristics: median GA [range] 28 + 6 [23 + 4–35 + 2], median birthweight [range] 1130 g [630–3710 g]) [55]. The likelihood of TBSS detecting an effect of the intervention on the FA will depend on the overall FA increase and its distribution around the mean FA increase. The effect of the current intervention on FA is unknown. We hypothesize that the increase in FA in the intervention group will be moderate, in the order of 5%. TBSS analyses the relation between different parameters (e.g., GA, sex, intervention group) and the FA of voxels of the white matter skeleton (i.e., the inter-subject aligned centre of white matter tracts). Based on the simulations in neonates reported by Ball et al., in order to detect an estimated increase in FA of 5% in approximately 50% of the TBSS skeletal voxels 35 infants per intervention group are required [55]. They showed that TBSS can detect clinically relevant global differences in FA, even in small groups and can therefore be used as a powerful biomarker of white matter development [55]. In a recent study comparing the effects of high vs. lower breast milk exposure in 20 vs. 27 preterm infants group wise differences in brain connectivity at TEA were shown with TBSS [61]. Based on these results we assume this whole-brain DTI analysis technique is sensitive to the effects of our intervention with 35 evaluable infants per intervention group. In total 70 evaluable infants will be needed. To account for potential drop-outs and non-evaluable infants, the target population should consist of 88 randomised infants. This number includes allocated twins/multiple births.

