### Statistical analysis

#### Primary outcome parameter and other MRI-derived parameters

TBSS analysis will be performed as previously described [61]. In summary, group comparisons will be performed with FMRIB Software Library’s Randomise tool using a general linear univariate model, [62] with family-wise error correction for multiple testing using threshold-free cluster enhancement with a significance level of *p* < 0.05 [63]. Group comparisons for volumetric analyses will be performed with ANOVA, with false discovery rate to correct for multiple testing. In all analyses GA at birth, postmenstrual age at time of MRI, birth weight Z-score and days of ventilation will be entered as covariates. These analyses have been used in several other observational and intervention studies conducted in the UMC Utrecht and other research groups, in preterm infants at TEA (mean and median GA of 28.7 weeks), [52, 64] healthy and asphyxiated full term infants, [65, 66] as well as children at school age (7.5–8.5 years and 12 years of age) [67–69].

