#### Safety and tolerance parameters, exploratory outcome parameters and secondary outcome parameters that are not derived from MRI assessment

Statistical analysis of continuous outcomes that are measured at more than one time point will be performed by means of linear mixed models analysis. Statistical analysis of discrete outcomes (dichotomous variables, ordered categorical variables and counts) will be performed using parametric (i.e., generalized linear models) or non-parametric methods. For other types of outcome parameters stratified tests (e.g., Cochran-Mantel-Haenszel test) and/or simple hypothesis testing methods (e.g., Chi-square or Fisher exact tests) will be employed. Details on the statistical analyses will be documented in a statistical analyses plan prior to database lock/unblinding.

Considering our relatively small sample size, it is possible that confounding factors for probiotic efficacy, such as antibiotic exposure, could be unevenly distributed between the active and placebo study group. Baseline characteristics will be evaluated at the start of the statistical analysis, and important confounding factors will be taken into account as covariates in the analysis. Analysis of the primary outcome parameter will be based on all included patients intended to treat with usable MRI according to DTI quality. Additionally, a per protocol analysis will be carried out for supporting purposes. Safety parameters will be analysed on the All Subjects Treated population. To account for possible cross contamination additional analyses will be performed to evaluate infants with and without *B. breve* M-16V colonisation. A *p*-value < 0.05 will be considered statistically significant.

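### Siblings always share an arm, but the stated MRI analyses and the 35-per-group sample size make no allowance for family, so the 5% level is exceeded if sibling outcomes correlate positively

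*Protocol article*

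**What the plan says.** Three parts of the Protocol article bear on this.

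- **Treatment allocation and blinding.** Randomisation is by permuted blocks, 1:1, stratified by sex, with the rule "Twins and multiple births will be allocated to the same study group". For multiples, the family is therefore the unit of allocation.
- **Sample size calculation.** From published simulations the article concludes that to "detect an estimated increase in FA of 5% in approximately 50% of the TBSS skeletal voxels 35 infants per intervention group are required". It continues: "In total 70 evaluable infants will be needed". The step to 88 is explained by losses alone: "To account for potential drop-outs and non-evaluable infants, the target population should consist of 88 randomised infants". On siblings it says only: "This number includes allocated twins/multiple births".
- **Statistical analysis, primary and other MRI outcomes.** The group comparison uses the "Randomise tool using a general linear univariate model", with family-wise correction at the 5% level. Volumes are compared by ANOVA with false discovery rate control. Four covariates apply throughout: gestational age, age at scan, birth weight Z-score and ventilation days. None identifies the mother.

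The section on non-MRI outcomes names linear mixed models for continuous outcomes with repeated measurements and generalized linear or non-parametric methods for discrete outcomes. For other types of outcome it names stratified tests and/or simple tests: "simple hypothesis testing methods (e.g., Chi-square or Fisher exact tests) will be employed". It refers details to a statistical analysis plan.

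**The concern.** A permutation test is valid when the rearrangements it uses are ones the randomisation could have produced. Shuffling infants one at a time puts siblings in different arms, which the allocation rule forbids. If siblings resemble each other, the shuffled data then show less between-arm variation than the real allocation generates, and p-values come out too small. ANOVA on individual infants has the same fault for the volumes.

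The covariates do not remove the problem. Siblings share gestational age, which is in the model. They also share a mother, prenatal exposures and usually a feeding choice, and none of these is in it. The article says that milk type follows the parents' choice (Supplementation), and it cites a TBSS difference by breast milk exposure in support of its sample size. Some positive residual correlation is therefore plausible on the article's own account.

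At stake are the error rate of the primary test in a small trial and the claim that 35 infants per group suffice.

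**Working it through.** **The plan's own figures.** The 35 per group cannot be rebuilt: it is read from outside simulations, and the article gives no standard deviation of fractional anisotropy (FA) and no power. The step from 70 to 88 can be checked. The implied loss is 1 − 70/88 = 20.5%, and 70/(1 − 0.20) = 87.5, rounded up to 88. The loss rate is not stated, but at 20% the whole inflation is used up and nothing remains for clustering.

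**Inputs for the illustration**
- n = 35 evaluable per group (Sample size calculation).
- Level 5% (Statistical analysis). Sidedness is not stated; two-sided is assumed.
- f, the share of evaluable infants whose twin is also evaluable: not in the article, assumed 0.1 to 0.5.
- ρ, the within-pair correlation after covariates: not in the article, assumed 0.2 to 0.8.

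**Formulas.** An arm of n infants contains nf/2 pairs. The variance of the sum is nσ² + 2·(nf/2)·ρσ² = nσ²(1 + fρ), so:
- design effect DE = 1 + fρ
- actual error = 2·[1 − Φ(1.96/√DE)]
- effective n = 35/DE

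**Middle case**, f = 0.3 and ρ = 0.5: DE = 1 + 0.15 = 1.15. Then 1.96/√1.15 = 1.828, which gives an error of 6.8%, and 35/1.15 = 30.4.

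The formula was checked by simulating a single test with 35 infants per arm and pairs kept together (4,000 trials, 399 permutations). Permuting infants singly was compared with permuting whole families among families of the same size.

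| f | ρ | DE | Error, formula | Effective n | Simulated error, infants permuted | Simulated error, families permuted |
|---|---|---|---|---|---|---|
| 0.1 | 0.2 | 1.02 | 5.2% | 34.3 | not run | not run |
| 0.2 | 0.4 | 1.08 | 5.9% | 32.4 | 5.9% | 4.8% |
| 0.3 | 0.5 | 1.15 | 6.8% | 30.4 | 6.7% | 4.8% |
| 0.3 | 0.8 | 1.24 | 7.8% | 28.2 | 7.7% | 4.8% |
| 0.5 | 0.8 | 1.40 | 9.8% | 25.0 | 9.7% | 5.0% |

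The simulation used whole pairs (4, 5, 5 and 9 per arm), so its twin shares are approximate: 8/35 = 23%, 10/35 = 29% twice, and 18/35 = 51%. With no twins, infant-level permutation gave 4.3%. The Monte Carlo standard error is about √(0.05 × 0.95/4000) = 0.34 percentage points.

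Formula and simulation agree, and permuting whole families restores the nominal level. The voxelwise family-wise error after threshold-free cluster enhancement was not simulated; the same exchangeability argument applies to it, in the same direction. Triplets would raise the design effect further.

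**The case against.** The best defence is that this is analysis-plan detail. The article summarises the TBSS method and points to a statistical analysis plan, which could specify family-level permutation. It never says that infants are independent or that siblings may be split. The reference to that plan sits under the non-MRI heading, but that section also fixes the primary analysis population, so the heading is a weak boundary. This softens the point about the test without removing it: the allocation rule and the analysis, followed as written, do not fit together. It does not touch the sample size, because a valid family-level test still works with less information than 35 independent infants give.

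The second defence is about size, and it stands. The share of multiples and the correlation are assumptions. Adjustment for gestational age, and for age at scan where siblings share it, lowers the residual correlation, and losses can break pairs. With few multiples or a low correlation the error is only about 5.2–5.5%.

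Two stronger readings are tempting, and the article supports neither.
- A reader might infer that every secondary and safety test is invalid. However, chi-square and Fisher tests are only examples for a residual class of outcomes, and the mixed and generalized linear models named for the rest can take a family term without contradicting the text.
- A reader might infer a definite loss of power or of a promised precision. The article states no power, standard deviation or interval width, so no such loss can be quoted. Whether the cohort behind the cited simulations included siblings cannot be checked here either.

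**Conclusion.** The point holds for the primary TBSS test, the volumetric ANOVA and the sample size statement. The direction is certain whenever sibling sets are enrolled and their residual outcomes correlate positively: the nominal 5% is exceeded, and 35 infants are worth fewer than 35 independent ones.

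The size is illustrative. Over the assumed ranges the single-test error runs from 5.2% to 9.8%. The middle-case 6.8% should not be read as this trial's type I error: it rests on an assumed 30% share and correlation of 0.5, and it is not the corrected voxelwise rate. For non-MRI outcomes the methods are open enough that a clarification is needed, not a correction of a proven error.

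**What to change.** **Primary and other MRI outcomes.** Define each mother as an exchangeability block and permute whole families among blocks of equal size. State how this respects "The permuted block randomisation will be stratified by sex (boys, girls) with a 1:1 allocation ratio of test and control product", since opposite-sex siblings span the two strata. For the volumes, add a random intercept for mother or use cluster-robust errors by mother.

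**Non-MRI outcomes.** State that the mixed and generalized linear models account for family (random intercept, generalized estimating equations or cluster-robust errors), and prefer these to chi-square or Fisher tests that ignore it.

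**Sample size.** State the sponsor's own assumed share of multiples and sibling correlation, and the effective sample size that follows. The figures above are assumptions and should not be copied into the protocol as fact.

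**Cost.** Wording, a block file for the permutation software, slightly wider intervals and a slightly less favourable sample size statement. No extra enrolment and no change to trial conduct. The change should be fixed before unblinding, so that it cannot look driven by the data.

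### Sex is the only stratification factor but is not among the covariates fixed for the MRI analyses; the cost is a small loss of precision, not a false-positive risk.

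*Protocol article*

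**What the plan says.** Three sections of the protocol article bear on this.

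- **Treatment allocation and blinding.** The design sentence reads: "The permuted block randomisation will be stratified by sex (boys, girls) with a 1:1 allocation ratio of test and control product". On assignment, the same section says: "Based on the order in which infants enter the study and stratified by sex, the infant will be assigned a randomisation number by the eCRF". It also has a rule for siblings: "Twins and multiple births will be allocated to the same study group". No stratification factor other than sex is named.
- **Sample size calculation.** In describing the method, it says: "TBSS analyses the relation between different parameters (e.g., GA, sex, intervention group) and the FA of voxels of the white matter skeleton".
- **Primary outcome parameter and other MRI-derived parameters.** For the primary outcome, "group comparisons will be performed with FMRIB Software Library’s Randomise tool using a general linear univariate model", with family-wise error correction; volumes are compared by ANOVA. Then: "In all analyses GA at birth, postmenstrual age at time of MRI, birth weight Z-score and days of ventilation will be entered as covariates". Sex is not in that list.

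The section on the non-MRI outcomes adds that baseline characteristics will be examined and important confounders taken in as covariates. It does not name sex. It mentions stratified tests only for outcomes other than MRI, and leaves further detail of those analyses to the SAP.

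**The concern.** An analysis should normally condition on the factors used to restrict the randomisation. Stratified blocks balance the arms on sex, so the sex effect largely drops out of the treatment difference. If the model ignores sex, that variance stays in the residual, and the standard error is then too large for the design used. The trial pays for stratification and does not collect the benefit.

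This is not a detail left to the SAP. The article states a specific list for all MRI analyses, and the list omits the one factor the design controls. It also sits uneasily with the sample size section, where sex serves as an example of a TBSS parameter. At stake is some precision for the primary FA comparison and the volumetric outcomes, in a trial that needs only 70 evaluable infants.

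**Working it through.** **The plan's own figures.** The article gives 35 evaluable infants per group, 70 in total and 88 randomised. With an assumed drop-out of 20% (no rate is stated), 70/0.80 = 87.5, rounded up to 88, so the inflation is reproducible. The 35 per group comes from simulations in a cited study. It cannot be reproduced, because neither an SD of FA nor a power is given. None of these figures is disputed here.

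**Inputs.** From the article: n = 35 per group and significance level 0.05. Assumed: a two-sided test, a single scalar outcome, a standardised difference d = 0.68 (chosen because a two-sample t test then has 80% power), and a share R² of residual variance explained by sex of 2%, 5% or 10%.

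**Gain from adding sex.** With sex balanced, adjustment shrinks the residual SD by √(1 − R²). The equivalent sample size is 35/(1 − R²) and the effective difference is 0.68/√(1 − R²).

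| R² of sex (assumed) | Equivalent n per group | Effective d | Power |
|---|---|---|---|
| 0 (sex not in model) | 35.0 | 0.680 | 80.1% |
| 2% | 35/0.98 = 35.7 | 0.687 | 80.9% |
| 5% | 35/0.95 = 36.8 | 0.698 | 82.0% |
| 10% | 35/0.90 = 38.9 | 0.717 | 84.0% |

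For scale: with equal numbers of boys and girls, R² = 10% needs a boy–girl difference of 2√(0.10/0.90) = 0.67 within-sex SD. That is about as large as the treatment effect assumed here. R² = 2% needs 2√(0.02/0.98) = 0.29 SD.

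**Check by simulation.** Assumed: 70 infants, blocks of 4 within sex, no twins, ordinary linear model, 6,000 runs per setting, treatment effect 0.67 SD for power and zero for type I error.

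| Sex effect | Power without / with sex | Type I error without / with sex |
|---|---|---|
| 0.2 SD | 78.5% / 78.7% | 4.9% / 4.9% |
| 0.5 SD | 77.8% / 79.4% | 3.9% / 4.5% |
| 0.8 SD | 73.6% / 78.1% | 3.8% / 5.1% |

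The loss is between nothing and about 5 percentage points of power. Type I error without sex stays below 5%: the error is on the conservative side.

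**Balance when siblings share an arm.** The simulation was repeated with 20% to 30% of infants as twins, 60% of pairs of the same sex, and the second twin given the first twin's arm (all assumed). Without twins, the arm difference within either sex never exceeded 2 infants. With twins it exceeded 2 in about 36% to 50% of trials, with a 95th percentile of 4 to 5. So exact within-sex balance cannot be taken for granted.

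**What adding sex does not do.** In the same twin settings, with a within-pair correlation of 0.5 (assumed) and no treatment effect, type I error in the sex-adjusted model was about 5.4% to 7.0%. Adjustment for sex leaves sibling correlation untouched.

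**The case against.** The strongest reply is that the harm is small and in the safe direction. The test stays valid, and for FA the gain is probably near the low end: at R² = 2% it is worth 0.7 of an infant per group and less than one point of power. No input to the power figures except n = 35 and the significance level comes from the article. The calculation is also for an ordinary linear model on one outcome, whereas the primary test is a voxelwise permutation test with cluster enhancement; the exact size there has not been shown. All of this stands, and it limits the weight of the point.

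Four stronger readings are tempting and are not supported.

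- **That the covariate list is closed, so any sex imbalance must go uncorrected.** The confounder provision stands under the non-MRI heading, but its paragraph goes on to the primary outcome and may well cover it. It is a possible route. But it depends on observed baseline differences, does not commit to sex, and would tend to pass over a factor that stratification has balanced.
- **That the sibling rule forces the sex-specific lists to be overridden and so breaks the blocks.** The article does not describe how siblings enter the sequence; one draw per family is possible. Only the narrower statement follows: siblings in one arm mean that exact balance within sex is not assured.
- **That the primary test is invalid.** Omitting sex does not raise type I error.
- **That the Bayley and growth models and the stratified tests are also at fault for not naming sex.** The article expressly leaves those details to the SAP.

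The sample size sentence is likewise a general description with examples, not a model specification, so the mismatch with the covariate list is an inconsistency to tidy rather than two conflicting models.

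**Conclusion.** The point holds in a limited form. The design stratifies by sex alone, and the covariates stated for all MRI analyses leave sex out without giving a reason. The consequence is a slightly conservative test and some lost precision. Under the assumed R² of 2% to 10%, adding sex moves power from 80% to between 81% and 84%; the simulation puts the loss from omission at about 0 to 5 points for sex effects up to 0.8 SD, with FA likely near the low end. These sizes rest on assumed sex effects, a two-sided test and an ordinary linear model. The case for change is that the remedy costs almost nothing, not that the present plan would mislead. Possible loss of exact within-sex balance through the sibling rule adds modestly to that case.

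**What to change.** In the section on the primary outcome and other MRI-derived parameters, add sex to the prespecified covariates of the TBSS model and the volumetric models, before unblinding and whatever the observed balance. Align the description in the sample size section with the final list. The present model uses an intercept, treatment and four covariates, leaving 70 − 6 = 64 residual degrees of freedom; with sex it leaves 63. No further data are needed, since sex is already recorded for randomisation. Correlation between siblings needs its own provision and should not be regarded as settled by this change.
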